## Abstract

**Background:**

Burn injuries remain a neglected public health issue in low-and middle-income countries (LMICs). Up to 90% of burn injuries occur in LMICs, where there is a lack of appropriate burn prevention, acute care and rehabilitation services. When co-created with target populations, health education and communication campaigns could play a pivotal role in promoting risk assessment and improving knowledge, attitudes and practices regarding first aid for burns in low-resource settings. Photovoice is a co-creation approach that engages target communities in capturing and communicating their lived experiences through photography. The present study protocol describes the design of a health education and communication campaign incorporating Photovoice to improve knowledge, attitudes and practices regarding burn injuries in Pakistan.

**Methods and analysis:**

This cohort study will follow 600 participants (*n* = 600; *n* = 500 burn survivors; *n* = 100 caregivers) with three measurement points at 6- to 12-month intervals. The primary outcomes are knowledge, attitudes and practices regarding burn injuries. The secondary outcomes are meaning in life; gratitude, resentment and appreciation; hope; optimism; temporal satisfaction with life; coping strategies; social interaction anxiety; self-stigma and resilience, measured using the Meaning in Life Questionnaire, the Gratitude, Resentment and Appreciation Scale, the Adult Workers Hope Scale, the Patient Optimism Scale, the Temporal Satisfaction with Life Scale, the COPE Inventory, the Social Interaction Anxiety Scale, the Self-Stigma Scale and the Brief Resiliency Scale, respectively. The participants are grouped as follows: the exposure group (i.e., burn survivors [*n* = 200] and caregivers [*n* = 100] exposed to campaign messages), the non-exposure group (i.e., burn survivors [*n* = 250] not exposed to campaign messages) and the Photovoice group (i.e., burn survivors [*n* = 50] who participate in Photovoice and are exposed to the campaign messages). This design evaluates the impact of the health communication campaign and determines whether Photovoice has any additional effects on the primary and secondary outcomes.

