### Research design

2.1

This study is a cohort study with three measurement points conducted at 6- to 12-month intervals (*n* = 600). The impact of the health communication campaign will be evaluated by measuring indicators of knowledge, attitudes and practices related to burn first aid, as well as psychological variables and health information-seeking variables, among the following groups: the exposure group (i.e., burn survivors [*n* = 200] and caregivers [*n* = 100] exposed to campaign messages), the non-exposure group (i.e., burn survivors [*n* = 250] not exposed to campaign messages) and the Photovoice group (i.e., burn survivors [*n* = 50] who participate in Photovoice and are exposed to the campaign messages). Figure 1 presents the campaign process and the planned activities in different phases.

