##### Knowledge Attitudes And Practice (KAP) Scale

2.2.5.1

The KAP includes a range of structured interviewer-administered questions to obtain a better understanding of knowledge, attitudes and practices regarding burn injuries (22, 34). The knowledge- and attitude-based questions include 10 items, scored on a four-point Likert scale ranging from strongly disagree to strongly agree. Higher scores represent better knowledge of and favourable attitudes toward burn injuries and first aid. The practice of burn first aid includes 12 questions with various response formats, such response categories such as ‘true/false’ and ‘yes/no’. A sample item for the knowledge-based questionnaire is, “Burns lead to permanent injuries?’ A sample item for the attitude-based questionnaire is, ‘Do you think that applying dough, oil, mud, toothpaste, etc. on the wound delays the healing process?’ A sample item for the practice of burn first aid is, ‘In case of a burn injury, have you ever applied cold water?’ The internal consistency, measured using Cronbach’s alpha, was 0.887 for the knowledge-based questionnaire, 0.716 for the attitude-based questions and 0.758 for the practical questions (22).

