##### Brief Resiliency Scale (BRS)

2.2.5.10

The BRS is a six-item self-report scale (47). Sample items include the following: ‘I tend to bounce back quickly after hard times’; ‘I have a hard time making it through stressful events’; ‘It does not take me long to recover from a stressful event’; and ‘It is hard for me to snap back when something bad happens’. The response options for all items are ordered on a five-point Likert-type scale. The scale demonstrated appropriate internal consistency, with Cronbach’s alphas ranging from 0.80–0.91 across four samples in the study (47).

The sample size calculation for the study is based on a comparison of the baseline and follow-up measures of the primary outcome, knowledge of burn-related prevention, in this cohort study. Using a previous study as a reference (22), we determined that a sample size of 478 is required to achieve a 70% improvement in knowledge of burn-related prevention, assuming a 63% rate of poor knowledge at baseline, a 5% significance level and 91.5% power at the 24-month follow-up (last follow-up). A total of 600 participants will be required, with a 20% dropout rate taken into account.

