## Data analysis plan

4

To compare changes in self-reported outcomes within groups across two time points (see Table 1) in the sample (*N* = 600), we will implement linear mixed-effects models implemented in R (R version 3.6.1) (51) using the lme4 package and in SAS 9.4. This method considers correlations within participants, allowing them to be modelled appropriately. It also estimates within-subject variability, in addition to estimating model parameters. The method can handle and model missing outcome data under the assumption that the data are missing at random. The mixed model uses a longitudinal data structure that includes both fixed and random effects, and baseline measurement is usually included as a covariate. Time will be included in the model as an interacting categorical variable to observe any time-varying trends. Cohen’s *d* for the effect of Photovoice will be calculated as the difference between baseline-corrected estimated means divided by the pooled standard deviation. A two-sided *p* < 0.05 indicates statistical significance. In addition, demographic variables, such as age, education, gender, marital status, geographic location (i.e., rural vs. urban residence) and household situation (i.e., living with a single and/or an extended family) will be included in the linear mixed models to test for potential moderating and mediating effects on behavioural intention related to burn prevention and first-aid practices. A stepwise selection of the variables will be conducted to determine which variables to keep in the model. As we add the variables, we will immediately eliminate those that do not reduce the Akaike information criterion (AIC) by using the *stepAIC* R function from the library *MASS*. If two or more independent variables in a model are found to be strongly correlated, a variance inflation estimate of less than 5 will be used to determine whether collinearity is present. If the relationship is found to be non-linear, attempts will be made to model the outcome data via the use of splines or polynomials in the *nlme* package in R. The normality of residuals will be assessed graphically using histograms and Q-Q plots. Detailed statistical analyses following Good Clinical Practice: Consolidated Guidelines ICH E9 (52) and Medical Research Council guidelines for developing complex interventions (53) will be described in the statistical analysis plan, which will be finalised before the data lock stage.

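### The protocol names three primary outcomes but sizes the study on one, so its 5% level and 91.5% power describe the study only if knowledge is the single primary outcome

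*Protocol article*

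**What the plan says.** The abstract (Methods and analysis) says: "The primary outcomes are knowledge, attitudes and practices regarding burn injuries". The second objective in section 1 likewise aims the campaign at all three.

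Section 2.2.5.1 describes one KAP instrument made up of separate question sets, with separate Cronbach's alphas: "0.887 for the knowledge-based questionnaire, 0.716 for the attitude-based questions and 0.758 for the practical questions". No single combined KAP score is defined.

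The sample-size paragraph, placed at the end of section 2.2.5.10 (Brief Resiliency Scale), uses the singular. It compares baseline with "follow-up measures of the primary outcome, knowledge of burn-related prevention, in this cohort study". The significance level, the power, the 63% baseline rate of poor knowledge and the 24-month last follow-up are all attached to that one outcome.

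Section 4 (Data analysis plan) gives one general rule: "A two-sided *p* < 0.05 indicates statistical significance". The article states no order among the three outcomes, no split of the significance level, and no rule on whether one significant outcome is enough or all three are needed. Section 4 leaves detailed analyses to a statistical analysis plan that is to be finalised before data lock and is not shown.

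**The concern.** The choice of primary outcome decides what the 5% and the 91.5% refer to. With knowledge alone as primary, both figures describe the study. With three primaries, at least one of them does not:

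- If success on any one outcome may be presented as campaign impact, the chance of at least one false positive among the three exceeds 5%.
- If success on all three is required, the error is controlled, but the power of the study is the chance that all three succeed. The article gives power for knowledge only.

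The sample size also depends on the answer, because dividing the 5% among three outcomes needs more participants than the planned 600. The definition should therefore be settled in the protocol before outcome data can influence the choice.

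**Working it through.** **Inputs from the article.** Three primary outcomes (abstract); one primary outcome, 5% level, 91.5% power, 63% baseline rate, 478 evaluable, 20% dropout, 600 recruited (section 2.2.5.10); two-sided 0.05 (section 4). The article gives no correlation between the three scores, so a range is assumed.

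**1. The plan's own figure.** The paragraph says "we determined that a sample size of 478 is required to achieve a 70% improvement in knowledge of burn-related prevention". The reading that comes closest is a one-sample test of 63% against 70%, two-sided 5%, with the variance taken at 70%:

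n = (z₀.₉₇₅ + z₀.₉₁₅)² × 0.70 × 0.30 / 0.07² = (1.960 + 1.372)² × 0.21 / 0.0049 = 475.9, so 476.

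This is within two participants of 478, and power at 478 is about 91.6%. For dropout, 478 / (1 − 0.20) = 597.5, so 598, rounded in the plan to 600. The calculation therefore uses one outcome at the full two-sided 5%, with nothing set aside for attitudes or practices. (The paragraph does not itself describe a one-sample test. That is a separate matter.)

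**2. Error if any one of three suffices, each at 0.05.**

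- Independent tests: 1 − 0.95³ = 14.3%.
- Bound with no assumption on correlation: 3 × 0.05 = 15%.
- Equally correlated normal test statistics, by simulation (one million draws):

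| Assumed correlation | Any false positive | False positive in the favourable direction only |
|---|---|---|
| 0 | 14.3% | 7.3% |
| 0.3 | 13.6% | 6.8% |
| 0.5 | 12.5% | 6.3% |
| 0.7 | 10.9% | 5.5% |
| 0.9 | 8.3% | 4.2% |
| 1 | 5.0% | 2.5% |

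The nominal rates to compare with are 5% and 2.5%.

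**3. Error and power if all three are required.** The error cannot exceed 5%, since every test must reject at 0.05. The power cannot exceed that of the weakest outcome. It cannot be calculated from the article, which gives no effect or power for attitudes or practices. As an illustration only, assume that each outcome had 91.5% power. Joint power would then lie between 1 − 3 × 0.085 = 74.5% and 91.5%, and would be 0.915³ = 76.6% under independence.

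**4. Three primaries with the level split equally.** Each is tested at 0.05/3 = 0.0167, with critical value 2.394. Familywise error is at most 5% (1 − (1 − 0.05/3)³ = 4.9% if independent). Power for knowledge at the planned size is Φ(1.960 + 1.372 − 2.394) = Φ(0.938) = 83%. Restoring 91.5% multiplies the sample size by ((2.394 + 1.372) / (1.960 + 1.372))² = 1.277. From a base of 476 to 478 this gives about 608 to 611 evaluable, or about 760 to 764 recruited at 20% dropout.

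**5. Knowledge as single primary outcome.** Error is 5%, and 478 and 600 stand as written.

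**The case against.** The best defence is that sizing a study on one of several primary outcomes is ordinary practice, that the singular in the sample-size paragraph is loose wording, and that ordering and multiplicity rules commonly sit in the statistical analysis plan. Much of this stands. The absence of a multiplicity procedure from a condensed article is not a fault, and a general threshold is not a statement that no adjustment will be made. It does not remove the conflict between two definitions of the primary outcome in the same article, one of which fixes the sample size.

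A reader might also infer more than the article supports:

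- **A 14% chance of a false campaign claim, as a fact.** This needs the any-one-suffices rule, which the article does not contain, and independence between scores from one instrument, which is unlikely. It also counts false findings in both directions; for false benefit alone the independence figure is 7.3% against 2.5%.
- **A larger count of confirmatory tests.** Six independent tests would give 1 − 0.95⁶ = 26.5%, but the article does not say that both follow-ups count as primary. Section 4 describes change within groups with time as an interacting factor and does not set out two confirmatory between-group contrasts. The Photovoice comparison is called preliminary and a pilot. The nine psychological scales, including the COPE subscales, are secondary, with no confirmatory claim attached.

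It is also fair to say that naming knowledge as primary does not by itself align the sample size, which uses a rate of poor knowledge, with the linear mixed models of section 4. That is a separate point. Finally, a single primary with a fixed sequence is one acceptable solution among several.

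**Conclusion.** The point holds as an internal contradiction. The abstract has three primary outcomes, the sample-size paragraph has one, and the 5% level and 91.5% power describe the study only under the second. The consequence depends on a decision rule that is not given. Error is about 11% to 14% if any one outcome suffices (assumed correlations 0.7 to 0; bound 15%; closer to 5% if the scores are almost perfectly correlated). It is at most 5% if all three are required, with the study's power then unknown. The documents do not show that the trial's error rate is 14%. The defect is moderate: it affects what may be claimed, and it can be settled at little cost before data lock.

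**What to change.** Make the abstract and the sample-size paragraph agree. The least costly way is to name knowledge at the last (24-month) follow-up as the single primary outcome, which the sample size already assumes. Then test attitudes, and after that practices, each at two-sided 5% and only if the preceding outcome is significant.

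Define the time point by the 24-month last follow-up and not by the label t2 alone. The footnote to Table 1 ties t2 to the closed exhibitions and goes on to t3 and t4. Section 2.1 plans "three measurement points conducted at 6- to 12-month intervals", so two intervals span 12 to 24 months and reach 24 only at the maximum. These statements should be reconciled at the same time.

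Cost: a change of text, with 478 and 600 unchanged. The real price is that attitudes and practices, which the objectives treat on a par with knowledge, lose any confirmatory claim if knowledge is not significant.

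If the investigators prefer three primaries, they should state whether one or all must succeed and restate the power to match. With an equal split of the level, power for knowledge is about 83% at 478, and about 760 to 764 recruited would be needed to restore 91.5%. Power for attitudes and practices would need its own assumptions.

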**Ethics and dissemination:**

Ethical approval was obtained from the Pakistan National Bioethics (Approval ID: NBC-985) and Manchester University Research Ethics Committees (Approval ID: 2023-18,027-31199). The results of this study will be distributed through public dissemination events, social media channels and peer-reviewed journals.

## Introduction

1

Globally, burn injuries are one of the top 10 causes of trauma and a leading contributor to premature mortality and years lived in disability (1). The World Health Organization states that approximately 11 million burns and 265,000 burn-related deaths contribute annually to what has been described as a ‘forgotten public health crisis’ (2). Additionally, up to 90% of burn cases occur in low- and middle-income countries (LMICs), where burn prevention, acute care and rehabilitation services are inadequate (2). More strikingly, young girls in LMICs are at higher risk of burns at home, particularly in the kitchen, with fire-related burns being the sixth leading cause of death among females aged 15 and 29 years (2, 3). Furthermore, data obtained from the Global Burden of Disease (GBD) 2019 study indicated that Asia had the most new burn cases in 2019, with a 19% increase relative to cases in 1990 (3,913,524.80 [95% UI 2,946,199.45–4,959,607.51]) (4). Additionally, Asia had the highest death cases in 2019 (57,202.37 [95% UI, 41,804.00–70,564.74]) (4). Even though over half of the global burn-related deaths are estimated to be in South Asia (3), burn injury is an under-researched topic in Pakistan (5). There is a lack of national high-quality epidemiological data representing the remote areas of Pakistan (5). Therefore, the existing epidemiological data is likely underestimate the true health burden in LMICs in general and Pakistan specifically, where injury surveillance systems are rare (6).

Incidents leading to burn injuries can be accidental and/or intentional (5–7). Domestic and work-related incidents are the main contexts in which intentional dowry burn injuries occur in South Asia (5–7). Dowry is property or money given by the bride’s family to the groom or his family at the time of marriage (8). The practice stems from the lack of economic power of young women in the traditional family system and perpetuates oppression and torture (9). Dowry disputes between families often lead to dowry burn injuries among young brides (9). Burn injuries are intentionally inflicted upon the young bride by the groom and/or his family by throwing acid or other corrosive substances on the bride (9). A lack of knowledge of safe work techniques, first aid, illiteracy, poor socioeconomic conditions and the dowry practice are contributing factors (5–9).

Burn injuries affect not only the individual but also their family and community. Burn survivors experience long-term physical, psychological and social consequences (8, 10, 11). Longitudinal and experimental studies indicate that preexisting mental health conditions in both burn survivors and caregivers are closely related to survivors’ rehabilitation and psychological outcomes (12, 13). Many burn patients experience functional limitations shortly after the burn incident, limiting their ability to return to work or daily activities (11, 14). Burn incidents also affect patients’ families. Both patients and family members are at risk of developing post-traumatic stress disorder (PTSD) and experiencing guilt, stigma and discrimination, thus adversely affecting their quality of life (8, 11, 14). In countries where physical appearance is highly valued, burn survivors are often subject to harassment and negative, judgmental words (15). They experience increased distress in response to burn scars and other physical changes, leading to lower negative body image, self-esteem and social isolation (15).

There have been significant advancements in clinical burn care, the successful implementation of preventative initiatives and increased public awareness in high-income countries (16, 17). These advancements have led to a significant decrease in burn injuries and an increase in appropriate, high-quality care (16). Nonetheless, many LMICs still lack effective preventive measures, leading to persistently high rates of burn injuries (18–20). These injuries often occur without access to even the most fundamental health care, which can lead to avoidable fatalities, disabilities and social stigmatisation (18–20). In Pakistan, despite a population of more than 225 million and a high estimated incidence of burn injuries, insurance coverage and rehabilitative services are limited; this includes inadequate initial management of burn wounds and insufficient mental health care, leading to high rates of post-burn complications, such as contractures, PTSD and Common Mental Disorders such as anxiety and depression (21). Additionally, there is a lack of awareness of burn incidents and the challenges that burn survivors and their caregivers endure (21, 22).

Social media has the potential to play a pivotal role in raising public awareness and providing critical information that can aid prevention, improve mental health and reduce stigma (23–25). Recent campaigns in high-income countries show the feasibility of social media (i.e., Facebook, Instagram and TikTok) as an ideal platform for engaging with a wide range of audiences and for delivering public health messages (24). In LMICs, health communication interventions incorporating mass media communication and visual elements demonstrate improvements in knowledge related to burn safety and first aid (3). Additionally, community-based health education sessions consisting of interactive workshops and consultations with the target communities have been shown to be feasible and acceptable strategies for improving knowledge of first aid and prevention in rural areas in Bangladesh (10, 19). Pakistan is an ideal location to implement a health education campaign incorporating social media, mass media communication and community health education sessions. There were approximately 71 million social media users in Pakistan as of January 2022, equivalent to 31% of the total population (25). Furthermore, evidence from a large-scale randomised control trial (RCT) (*N* = 18,554) evaluating the impact of a health education intervention on heat-related outcomes and literacy demonstrated the feasibility and effectiveness of the intervention. The intervention was found to be effective in reducing hospital visits and enhancing heat literacy when compared to the control group receiving usual care in Pakistan (26).

Although education–media interventions show promise in reaching large populations in low-resource contexts and improving knowledge-related outcomes, several limitations restrict their impact. Most are small educational initiatives and lack sufficient long-term follow-ups (3). There is also little focus on involving the target communities during the process of developing and implementing such campaigns (3). To increase the reach and impact of health communication interventions, campaigns must be relevant, appropriate and implemented in collaboration with the target population (27). Hence, co-creation enables researchers to establish partnerships with community members and stakeholders, working together to identify research priorities throughout the process (27). This approach yields data that reflect community experiences, ensuring appropriateness and meaningful impact (27). This is essential to improve knowledge related to burn safety and reduce burn-related stigma globally (23).

One such co-creation approach is Photovoice (28). This method uses photography as a powerful channel to communicate individuals’ lived experiences to a broader audience and destigmatise chronic health and mental health conditions (28–32). Recent meta-analytic evidence of the health care literature showed that Photovoice is especially effective in improving health knowledge among ethnic minority groups in high-resource settings (32). Empirical evidence suggests that when Photovoice was delivered through Instagram, there were both significant immediate and long-term improvements in meaning, appreciation of others and life satisfaction (33). Photovoice has been implemented in high- and low-resource settings to explore the drivers of burn injuries and post-burn experiences of burn survivors (15). Overall, the existing literature highlights the flexibility of Photovoice as a community-based participatory approach applicable to various health conditions in different settings (15). More importantly, Photovoice helps identify the impact of the broader social context, such as stigma, on participants’ experiences; it highlights how social awareness of burn survivors’ needs and burn first aid knowledge is crucial for preventing burn incidents and addressing stigma at a societal level (15). Therefore, it is essential to design a health communication intervention to increase awareness, prevent burn cases and reduce negative social responses in order to improve the mental, emotional and physical quality of life of burn survivors and their relatives in Pakistan. Importantly, burn-mitigating techniques should focus on applying tried-and-tested solutions to promote risk assessment in several settings, such as households, schools and workplaces. These interventions should also improve knowledge, attitudes and practices regarding first aid for burns in LMICs in general and in Pakistan in particular.

The present study is one of the work packages of a larger research programme entitled ‘Burns rehabilitation: A multidisciplinary programme for burns management, treatment and prevention in low-income countries. The project is funded by the National Institute of Research (NIHR) under NIHR Research and Innovation for Global Health Transformation Call 4. The work packages (WPs) of the programme are as follows: understanding the context and intervention co-development (WP1); development and implementation of a national burn registry (WP2); clinical and cost-effectiveness evaluation of the burns care and rehabilitation programme in Pakistan compared to usual care (WP3); development and evaluation of a social media campaign to promote burn prevention and reduce burn-related stigma (WP4); engagement with key informants and policymakers to better understand, prevent and manage burn-related injuries (WP5); and development of sustainable capacity and capability in treatment and rehabilitation for burn injuries and research (WP6). The proposed health education social media campaign, informed by the WP1 findings, will be embedded within WP5 and WP6 to guide policies on burn prevention and management, along with initiatives for capacity and capability building in Pakistan.

The study uses Photovoice to develop and evaluate a collaborative, population-level health education and communication campaign aimed at improving burn prevention and first aid knowledge while reducing burn-related stigma for burn survivors in Pakistan. The campaign will be disseminated through social media platforms to increase its reach and scalability in Pakistan. The present campaign will be the first to evaluate the immediate, medium and long-term effects of the initiative on burn-specific knowledge and on the psychological well-being (meaning, gratitude, life satisfaction, resilience, etc.) of the participants (burn survivors, caregivers, health and emergency care professionals and key informants) in the Photovoice process and subsequent interventions.

The main objectives of this study are as follows:

Co-create a health education and communication campaign with the target population through Photovoice and health education sessionsAssess the short- and long-term effects of the campaign on improving knowledge, attitudes and practices regarding burn injuries in PakistanAssess the preliminary effects of Photovoice on improving knowledge, attitudes and practices regarding first aid and on reducing stigma toward burn injuries among burn survivorsPromote burn prevention and improve risk assessment in workplaces/factories through the health education and communication campaign

